Within 1 hour of stool sample arriving at the laboratory site, lab technicians will prepare from each sample a TSET assay, and 2 KK thick-smear slides (differentiated as Slide A and Slide B; see [Figure 1](#) for schematic flow chart and Peru KK2.0 Laboratory Protocol for a narrative description). One technician will prepare the sample for TSET and count the number of *A. lumbricoides*, *T. trichiura*, hookworm eggs, and any other additional identifiable parasites. This will provide qualitative data for later analysis. Two other lab technicians, using the same homogenized stool sample, will prepare the 2 KK thick-smear slides, Slide A and Slide B. Slides A and B will be analyzed within the first 30 minutes ( $\pm 10$  minutes) of slide preparation, in order to count hookworm eggs. Hookworm eggs will clear (ie, eggs will hatch) and disappear from stool samples within this window of time. Slide A will be analyzed via the KK1.0 method that uses manual counts of *A. lumbricoides*, *T. trichiura*, hookworm eggs, and any other identifiable parasites in the 30-minutes timeframe, and Slide B via the KK2.0 method that uses automated egg counts. Slide B will be loaded into the AI-DP slide scanner (aka KK2.0 method) and the system will automatically collect images of the slide. An on-board AI program will process the images, identifying eggs for verification. The slide images and identified eggs will be later uploaded to a cloud database and subsequently uploaded to the study database. See KK2.0 AID2STOP User Manual.

Slide B will be refrigerated overnight to allow the sample to become clearer from sediment and debris so that *A. lumbricoides* and *T. trichiura* eggs can be more easily identified. At the  $24\pm 4$ -hour timepoint, Slide B will undergo a manual (KK1.0) and digital (KK2.0) egg count. Slides will be randomly selected for the KK1.0 method first or KK2.0 method second, or vice versa.

All slides read by the KK1.0 method will be converted to eggs per gram (EPG) of stool statistics and uploaded to the study database. The images of all slides scanned into the AI-DP tool will be uploaded to the EggInspector application (see EggInspector Quick Start Guide) in the cloud database which will identify the eggs and the images will be validated by an expert parasitologist in Peru. Validated results will be uploaded to the study database.

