### **4.2. Measure to Minimize Bias**

To reduce potential bias during data collection and evaluation, at the 24-hour timepoint slides will be randomly selected for the manual counting (KK1.0 method) first or the KK2.0 slide scanning method second, or vice versa. Randomization will be conducted via sealed envelopes containing a code assigned to the method, ie, KK1.0 or KK2.0, that the lab technician will use first when reading Slide B. Each day the technicians will have 12 Slide Bs to read. They will select an envelope and follow the order of which method to use first and second when reading Slide B.

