### 4.3. Data Analyses

#### 4.3.1. Data Analyses

Descriptive summaries will be provided by diagnostic method and STH species. All continuous variables will be summarized using descriptive statistics, which will include the number of children, mean, standard deviation, median, minimum, and maximum. A 95% confidence interval (CI) will also be provided for EPG and sensitivity. All categorical variables will be summarized using frequencies and percentages. Summary and analysis will be provided by diagnostic method, STH species, and timepoints (30 minutes and 24 hours). It should be noted that at the 24±4-hour timepoint the same slide (Slide B), will be evaluated by both the KK1.0 and KK2.0 methods. While at the 30-minute timepoint, different slides (slides A and B) from the same stool sample will be evaluated by the same 2 methods. Therefore, extra caution should be exercised when comparing results from the different methods at the 30-minute timepoint since 2 different slides are being analyzed.

Egg load will be classified into 3 intensity categories as detailed below according to EPG:

- *A. lumbricoides*: Low: <5,000 EPG; Moderate: 5,000-49,999 EPG; Heavy: >50,000 EPG
- *T. trichiura*: Low: <1,000 EPG; Moderate: 1,000-9,999 EPG; Heavy: >10,000 EPG
- Hookworms: Low: <2,000 EPG; Moderate: 2,000-3,999 EPG; Heavy: >4,000 EPG

Since TSET method cannot produce EPG, intensity of each STH species will only be derived for KK1.0 and KK2.0 methods.

Since no “gold” standard for egg counts exist in this study, a diagnostic pseudo “gold” standard will be created. A sample is considered to be truly positive if any diagnostic method comes back with a positive reading at any time of the study.

Number of total positive samples for a STH species is defined as

$$N(+) = N(KK1.0(+))_{30m} \cup KK2.0(+))_{30m} \cup KK1.0(+))_{24h} \cup KK2.0(+))_{24h} \cup TSET(+))$$

Where  $KK1.0(+))_{30m}$  indicates a positive sample based on KK1.0 at 30 minutes,  $KK2.0(+))_{30m}$  indicates a positive sample based on KK2.0 at 30 minutes,  $KK1.0(+))_{24h}$  indicates a positive sample based on KK1.0 at 24 hours,  $KK2.0(+))_{24h}$  indicates a positive sample based on KK2.0 at 24 hours, and  $TSET(+))$  indicates a positive sample based on TSET which is performed only once during the study.

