#### Analysis of Primary Endpoints

Summary of EPG will be provided by diagnostic method, STH species, and timepoint. A permutation test (5,000 iterations) will be employed for comparison of EPG between different diagnosis methods (KK1.0 and KK2.). The 95% CI will be determined based on bootstrap analysis (5,000 iterations). To preserve the correlation of egg count readings by different diagnostic methods from either different samples or same smear of the same participant, permutations will be done within each participant, not across all participants (ie, in a permutation, once an egg count

reading is randomly assigned to one of the 2 diagnostic methods, the other reading from the same participant will be automatically assigned to the other diagnostic method). Re-sampling in bootstrap will be performed at participant level, and the egg count reading will remain with the same diagnostic method as performed.

Sensitivity for KK1.0 at 30 minutes will be calculated as

$$= \frac{N(KK(1.0(+))_{30m})}{N(+)}$$

Where  $N(KK1.0(+))_{30m}$  is the number of positive samples based on KK1.0 method at 30 minutes. Sensitivity for other diagnostic methods and other timepoints will be calculated similarly.

A permutation test (5,000 iterations) will be employed for comparison of sensitivity between different diagnosis methods and the 95% CI will be determined based on bootstrap analysis (5,000 iterations) in similar approach as for EPG. Sensitivity will be calculated for each of the 5,000 iterations, and p-value and 95% CI will be constructed.

Summary of percentages of SAC with low, moderate, or heavy infection intensity will be provided.

2x2 (eggs, no eggs) and 3x3 (low, moderate, or heavy infection intensity) tables based on egg load will be provided to evaluate agreement between different test methods. Weighted Kappa statistics will be provided.

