**SLIDE A - KK1.0 (30 + - 10 min)****(All Parasites Egg N°)**

| Factor |        |        |
|--------|--------|--------|
| 8      | 1
2 | 2
4 |

| Stool
TYP
E        |
|--------------------------|
|  |

1= Normal, formed  
(24)

2 = Pasty (12)

3= NON-LIQUID  
Diarrhea (8)Star  
t

|                          |                          |   |                          |                          |
|--------------------------|--------------------------|---|--------------------------|--------------------------|
|  |  | : |  |  |
| H                        | H                        |   | m                        | m                        |

End

|                          |                          |   |                          |                          |
|--------------------------|--------------------------|---|--------------------------|--------------------------|
|  |  | : |  |  |
| H                        | H                        |   | m                        | m                        |

Nega  
tive

|     |
|-----|
| Yes |
|-----|

Cont  
rol

|             |        |
|-------------|--------|
| Y
e
s | N
o |
|-------------|--------|

|                          |                          |                          |                          |                          |                          |                          |                          |                          |                          |                          |                          |                          |                          |                          |                          |
|--------------------------|--------------------------|--------------------------|--------------------------|--------------------------|--------------------------|--------------------------|--------------------------|--------------------------|--------------------------|--------------------------|--------------------------|--------------------------|--------------------------|--------------------------|--------------------------|

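### At 30 minutes KK1.0 always reads Slide A and KK2.0 always reads Slide B, so smear and method are fully confounded in the comparison assigned to hookworm

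*Protocol*

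**What the plan says.** Protocol Section 3.1.1 (and the synopsis) describes the preparation: "Two other lab technicians, using the same homogenized stool sample, will prepare the 2 KK thick-smear slides, Slide A and Slide B". It then fixes the 30-minute readings for every child. For the microscope, "Slide A will be analyzed via the KK1.0 method that uses manual counts of" the three STH species and other parasites; for the scanner, "and Slide B via the KK2.0 method that uses automated egg counts". The Sample Processing Form (Attachment 1) agrees: its 30-minute manual-count block is headed for Slide A.

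The only randomisation is in Section 4.2: "at the 24-hour timepoint slides will be randomly selected for the manual counting (KK1.0 method) first or the KK2.0 slide scanning method second", or the reverse. It concerns one slide, Slide B, on day 2.

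Section 4.3.1 recognises that the 30-minute readings come from different smears and says that "extra caution should be exercised when comparing results from the different methods at the 30-minute timepoint since 2 different slides are being analyzed". The analysis of primary endpoints then makes no distinction between timepoints: "A permutation test (5,000 iterations) will be employed for comparison of EPG between different diagnosis methods", with the two readings swapped within each child, a bootstrap 95% CI, and the same approach for sensitivity.

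The primary objective in Section 2 pairs hookworm with 30 minutes, and *Ascaris* and *Trichuris* with 24 hours.

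**The concern.** A within-child label swap asks whether the two readings could equally well have come from either method. At 24 hours both methods read the same smear, so the question is about the method. At 30 minutes, swapping the label also swaps the smear. If A and B smears differ systematically, for instance in smear order or thickness, that difference goes entirely into the KK2.0 versus KK1.0 contrast. No analysis of the 30-minute data can take it out again, because no child contributes the opposite pairing.

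What is at stake is the 30-minute EPG comparison, above all for hookworm. Section 3.1.1 says hookworm eggs disappear from the sample in this early window, so the 24-hour same-slide comparison is a weak substitute. The point estimate and the bootstrap CI are affected as well as the p-value: if the readers are identical and Slide B holds a fraction r of Slide A's eggs, the KK2.0/KK1.0 egg ratio estimates r.

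**Working it through.** The protocol gives no figure to reproduce: the 500 children are a pragmatic number, and no prevalence, egg load, slide variability or significance level is stated. The confounding follows from the text alone; the size can only be illustrated.

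**Step 1: allocation.**

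| Timepoint | KK1.0 reads | KK2.0 reads | Randomised |
|---|---|---|---|
| 30 min | Slide A, always | Slide B, always | nothing |
| 24 h | Slide B | Slide B | reading order |

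**Step 2: hand approximation.** Assume n infected children, mean m eggs per slide with gamma shape k = 0.4 between children, slide CV c, identical readers, and Slide B holding (1+δ) times Slide A's eggs. Then E[μ²] = m²(1+1/k). Each infected child contributes an expected difference δm, and

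E[d²] ≈ m(2+δ) + c²E[μ²](1+(1+δ)²) + δ²E[μ²].

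The standardised shift is z = nδm / √(n·E[d²]).

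- *30% infected* (n = 150), m = 30, c = 0.30, δ = 0.10: E[μ²] = 900 × 3.5 = 3,150. E[d²] ≈ 63 + 626.5 + 31.5 = 721. z = 450/√(150 × 721) = 450/328.9 = 1.37. Two-sided 5% rejection ≈ P(Z > 0.59) ≈ 28%.
- *5% infected* (n = 25), m = 10, c = 0.50, δ = 0.10: E[μ²] = 350. E[d²] ≈ 21 + 193.4 + 3.5 = 217.9. z = 25/√(25 × 217.9) = 25/73.8 = 0.34. Rejection ≈ 5.3% + 1.1% ≈ 6%.

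**Step 3: simulation of the permutation test.** 500 children, no true method effect, two-sided 5%, fixed pairing. Ranges cover slide CV 30–50%.

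| Infected, mean eggs | Slide effect 10% | Slide effect 20% |
|---|---|---|
| 30%, 30 | 15–30% | 42–77% |
| 10%, 30 | 9–14% | 18–37% |
| 10%, 10 | 7–11% | 19–31% |
| 5%, 10 | 7–8% | 9–17% |

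Repeat runs move individual cells by a few points; with 800 trials the standard error at 30% is √(0.3 × 0.7/800) = 1.6 points. The highest value seen for a 10% effect was about 32%. With no slide effect, the fixed pairing holds its level (4.0% and 4.9% in the first row's scenario). With random smear-to-method allocation the rate is 4.3–6.4% in all cells of that scenario.

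**Step 4: a second set of assumptions.** Mean 20 eggs, between-child shape 0.5, smear shape 5 (CV = 1/√5 = 45%), prevalence 10/20/40%. If Slide B recovers 90% of Slide A's eggs, EPG rejection is 10.7/17.3/28.3%; at 80% it is 29/54/79%. The median KK2.0/KK1.0 egg ratio is about 0.90 and 0.80 respectively. Randomising the pairing returns the ratio to about 1.00 and rejection to about 4–7%.

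**Step 5: sensitivity.** In the same runs, the apparent sensitivity difference is about 1 percentage point at 90% recovery and about 2 points at 80%, where the sensitivity test rejects in 2–8% of trials. Across all scenarios with a 10–20% slide effect the shift is about 1–3 points.

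**The case against.** The strongest reply is that the bias is assumed. Both smears come from one homogenised stool, and nothing in the protocol states or implies a systematic A/B difference of any size. Random smear-to-smear variation adds noise but no bias, and with no slide effect the fixed-pairing test holds its level. This stands: fixed pairing does not make the test invalid. It leaves exchangeability as an unprotected assumption.

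The protocol also discloses the two-slide problem, calls the study descriptive and exploratory, and prespecifies no hypotheses. That lowers the stakes. But p-values and CIs are still planned for this contrast, and the descriptive egg ratio would carry the same bias. Advice to be cautious cannot separate two aligned factors.

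Three stronger readings are tempting and are not supported:

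- *The result would reflect which technician made the smear.* Section 3.1.1 says two technicians prepare the two slides. It does not say that each is tied to a slide letter or that they do not rotate. The laboratory protocol it refers to is not at hand and may settle this. Rotation would remove a preparer effect, but not a smear-order effect.
- *The study has no other hookworm comparison.* The 24-hour Slide B count on Attachment 1 has a hookworm field, and summaries by species are planned at both timepoints. On the protocol's own account that reading is weak for hookworm, but it exists.
- *The sensitivity results are equally exposed.* They are not; see Step 5. Section 2 names sensitivity as the study's intent, so this limits the damage.

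**Conclusion.** The point holds for the 30-minute comparison, mainly for EPG. Smear and method are completely confounded there, by explicit text and under no assumption. Whether this biases the result depends on a systematic A/B difference that the protocol neither shows nor rules out.

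If such a difference exists and the methods read identically, the EPG test would reject in about 7–32% of trials for a 10% difference and about 9–77% for 20%, given 5–30% infected, mean 10–30 eggs per slide and slide CV 30–50%. These inputs are assumptions, and the figures show order of magnitude only; at low prevalence and low egg counts the excess over 5% is small. The 24-hour comparison, where both methods read Slide B, is not affected. The change is worth making before sampling starts, because no later analysis can recover what the allocation did not separate.

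**What to change.** In Sections 3.1.1 and 4.2, extend the sealed-envelope draw to the 30-minute reading. After both smears are made, the envelope decides which goes to the microscope and which to the scanner. The scanned smear is then labelled Slide B and kept for the 24-hour readings, so the day-2 procedure is unchanged. Record the draw and the preparer of each smear on Attachment 1. In Section 4.3.1, state that the 30-minute permutation test follows this randomisation.

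The cost is one extra draw per sample (about 500) and two more entries on the form, with no additional slides, readings or staff. One practical constraint needs care: slide labels and the QR code (Section 8.2) must be placed after the draw, and the reading must still fall within the 30 ± 10-minute window.

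If the draw cannot be added, Section 4.3.1 should say that the 30-minute difference combines smear, possibly preparer, and method, and should present it without a p-value.

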Within 1 hour of stool sample arriving at the laboratory site, lab technicians will prepare from each sample a TSET assay, and 2 KK thick-smear slides (differentiated as Slide A and Slide B). One technician will prepare the sample for TSET and count the number of *A. lumbricoides*, *T. trichiura*, hookworm eggs, and any other additional identifiable parasites. This will provide qualitative data for later analysis. Two other lab technicians, using the same homogenized stool sample, will prepare the 2 KK thick-smear slides, Slide A and Slide B. Slides A and B will be analyzed within the first 30 minutes (+/- 10 minutes) of slide preparation, in order to count hookworm eggs. Hookworm eggs will clear (ie, eggs will hatch) and disappear from stool samples within this window of time. Slide A will be analyzed via the KK1.0 method that uses manual counts of *A. lumbricoides*, *T. trichiura*, hookworm eggs, and any other identifiable parasites in the 30-minutes timeframe, and Slide B via the KK2.0 method that uses automated egg counts. Slide B will be loaded into the AI-DP slide scanner (aka KK2.0 method) and the system will automatically collect images of the slide. An on-board AI program will process the images, identifying eggs for verification. The slide images and identified eggs will be later uploaded to a cloud database and subsequently uploaded to the study database.

Slide B will be refrigerated overnight to allow the sample to become clearer from sediment and debris so that *A. lumbricoides* and *T. trichiura* eggs can be more easily identified. At the 24±4-hour timepoint, Slide B will undergo a manual (KK1.0) and digital (KK2.0) egg count. Slides will be randomly selected for the KK1.0 method first or KK2.0 method second, or vice versa.

All slides read by the KK1.0 method will be converted to eggs per gram (EPG) of stool statistics and uploaded to the study database. The images of all slides scanned into the AI-DP tool will be uploaded to the EggInspector application in the cloud database which will identify the eggs and the images will be validated by an expert parasitologist in Peru. Validated results will be uploaded to the study database.

Following data collection and upload to the study database, data will undergo quality control, cleaning, and eventually database lock. Ten percent of all slides (ie, KK1.0 and TSET) and 100% of KK2.0 will undergo quality control at each timepoint, where they will be recounted for eggs at the end of the day.

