| To assess the diagnostic performance of KK2.0 in comparison to KK1.0 at detecting hookworms ( Necator americanus and Ancylostoma duodenale ) and Ascaris lumbricoides and Trichuris trichiura in SAC living in selected areas of Ucayali, a remote Amazonian region of Peru, at the 30-minute and 24-hour timepoints, respectively, of slide preparation. | 
 
Eggs per gram (EPG)
 
Sensitivity of KK1.0 and KK2.0 at 30-minute and 24-hour timepoints
 
Agreement in KK1.0 and KK2.0 results at 30-minute and 24-hour timepoints
 
Percentages of SAC with low, moderate, or heavy intensity of infection by EPG
 
 |
| Secondary                                                                                                                                                                                                                                                                                                                                                                      |                                                                                                                                                                                                                                                                                                                            |
| To evaluate the prevalence STH (hookworms [ Necator americanus and Ancylostoma duodenale ], and Ascaris lumbricoides and Trichuris trichiura ) in the selected endemic, remote Amazonian region of Ucayali, Peru.                                                                                                                                         | 
 
STH prevalence as a percentage in SAC living in the selected areas of Ucayali, Peru
 
                                                                                                                                                                                      |

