|  | +       |  | +         |  | +          |  | + |  | + |  | + |                          |   |                          |   |                          |   |                          |   |

**Slide Preparation (time for 2 slides, Slide A and B)**Sta  
rt

|                          |                          |   |                          |                          |
|--------------------------|--------------------------|---|--------------------------|--------------------------|
|  |  | : |  |  |
| H                        | H                        |   | m                        | m                        |

E  
n  
d

|                          |                          |   |                          |                          |
|--------------------------|--------------------------|---|--------------------------|--------------------------|
|  |  | : |  |  |
| H                        | H                        |   | m                        | m                        |

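### At the 30-minute hookworm comparison, time since slide preparation and reading method can be confounded: the reads may be up to 20 minutes apart, and nothing matches or randomises their timing

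*Protocol*

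**What the plan says.** The Synopsis (Study Design) sets the first-day window: "Slides A and B will be analyzed within the first 30 minutes (+/- 10 minutes) of slide preparation, in order to count hookworm eggs". Section 3.1.1 repeats it and adds: "Hookworm eggs will clear (ie, eggs will hatch) and disappear from stool samples within this window of time". At this timepoint the method is fixed by slide. Slide A is counted manually, "and Slide B via the KK2.0 method that uses automated egg counts".

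The primary objective in Section 2 names hookworm first, then *A. lumbricoides* and *T. trichiura*, and places them "at the 30-minute and 24-hour timepoints, respectively, of slide preparation". Thirty minutes is therefore the hookworm timepoint.

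Section 4.2 limits the randomised order to the second day: "at the 24-hour timepoint slides will be randomly selected for the manual counting (KK1.0 method) first or the KK2.0 slide scanning method second". Section 4.3.1 gives one warning about the first-day comparison: "extra caution should be exercised when comparing results from the different methods at the 30-minute timepoint since 2 different slides are being analyzed". It does not mention reading time.

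In Attachment 1, one start and one end time serve both slides, under the label "Slide Preparation (time for 2 slides, Slide A and B". The Slide A manual read at 30 minutes has its own start and end time. The only legible KK2.0 block is the 24-hour one.

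**The concern.** By the protocol's own account, the hookworm count depends on when within the window a slide is read. Each slide may be read anywhere in that window, and no rule links the reading time of Slide A to that of Slide B from the same child. Since each slide always goes to the same method, a regular difference in timing would look the same as a difference in reading ability.

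Two kinds of harm are possible. If one method is regularly read later, it loses hookworm eggs and hookworm positives for a reason unrelated to the method, and the EPG and sensitivity comparisons are biased. The within-child permutation test in Section 4.3.1 would not protect against this. It treats the two readings as exchangeable when the methods are equal, and a systematic time gap breaks that. If the gaps go in both directions, they largely cancel in the averages but still lower agreement between methods, which is itself a primary endpoint.

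**Working it through.** The protocol gives no figure for this effect, so there is nothing to reproduce. The check has two parts.

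**1. The largest gap.** The window is 30 ± 10 minutes after preparation, from 30 − 10 = 20 to 30 + 10 = 40 minutes. The largest gap between the two reads is 40 − 20 = 20 minutes. If the wording is taken literally as any time up to the limit, the window is 0 to 40 minutes and the gap can reach 40. The rest uses 20.

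**2. What a gap could do when the methods are equal.** The inputs below are assumptions, because the protocol states neither a loss rate nor an expected egg count:
- L: share of visible hookworm eggs lost over 20 minutes, taken as 5%, 25%, 50% or 90%, with exponential loss.
- m: mean eggs per slide at the earlier read, with Poisson counts, taken as 1, 5 or 20. With the form's factor of 24 for formed stool these are 24, 120 and 480 EPG, all inside the protocol's low-intensity class for hookworm (below 2,000 EPG).

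The formulas are:
- EPG ratio, later to earlier: r = (1 − L)^(gap/20)
- False difference in detection: exp(−m·r) − exp(−m)

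Worked example for L = 50%, gap 20, m = 1: r = 0.50. Detection is 1 − exp(−1) = 63.2% at the earlier read and 1 − exp(−0.5) = 39.3% at the later one, a difference of 23.9 points.

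| L over 20 min | EPG ratio, 20-min gap | m = 1, 20-min gap | m = 5, 20-min gap | m = 20, 20-min gap | m = 1, 5-min gap |
|---|---|---|---|---|---|
| 5% | 0.95 | 1.9 | 0.2 | 0.0 | 0.5 |
| 25% | 0.75 | 10.4 | 1.7 | 0.0 | 2.6 |
| 50% | 0.50 | 23.9 | 7.5 | 0.0 | 6.3 |
| 90% | 0.10 | 53.7 | 60.0 | 13.5 | 20.2 |

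The last four columns are percentage points of false difference. A middle case at m = 3 gives 95.0% detection at the earlier read. If 10%, 20% or 30% of eggs are lost per 10 minutes, the means after 20 minutes are 3 × 0.81 = 2.43, 3 × 0.64 = 1.92 and 3 × 0.49 = 1.47. Detection is then 91.2%, 85.3% and 77.0%, which is about 4, 10 and 18 points lower.

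With a gap of zero, r = 1 and the false difference is 0 at every loss rate. Matching the read times therefore removes the artefact without needing to know the rate.

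**The case against.** **The gap is permitted, not imposed.** A reader might infer that the plan will report a time difference as a method difference. The documents do not support that. One slide goes to a microscope and the other to a scanner, so the two can be read in parallel. Nothing says that scans queue or run later, and neither scan duration nor the number of devices is stated. Bias needs a regular gap in one direction, and none is documented. This stands. It limits the point to a possibility that the design leaves open.

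**The form.** A reader might also infer that the form omits the 30-minute scan time. That cannot be shown. Parts of Attachment 1 are lost in the available text, including the heading and most items of the main sedimentation block and some quality-control fields. Figure 1, the laboratory protocol and the scanner manual are not available either. The images are collected automatically, so a timestamp may exist. What stands is narrower: the protocol does not state that this time is recorded or transferred to the study data.

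**The numbers.** They rest on chosen loss rates and egg counts, and the larger ones apply the maximum gap in one direction to every sample. None of them is an expected bias.

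**The study is descriptive and already urges caution.** No hypotheses are prespecified. However, Section 4.3.1 plans p-values and confidence intervals for the comparison, and a confounded contrast misleads in a descriptive report too. The existing caution concerns two different slides, not two different times.

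**An adjustment could be left to the SAP.** It could, but only if both elapsed times are collected, and that is a matter for the protocol and the form.

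**Conclusion.** The point holds as a risk of confounding. At the timepoint that the primary objective assigns to hookworm, method is tied to slide, the reads may be up to 20 minutes apart in a window where the protocol says the eggs disappear, and neither matching nor random order is required. The protocol does not state that the time needed to check for this is captured on the KK2.0 side.

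The size cannot be determined from the documents. At the full gap it runs from negligible (0.2 points or less at 5% loss with a mean of 5 or more eggs per slide) to dominant (over 50 points at 90% loss with a mean of 1 to 5). This assumes Poisson counts, exponential loss and a gap in the same direction for every sample. Shorter or mixed gaps give less bias. At the low to moderate loss rates the effect is largest at the lowest egg counts. The conclusion does not extend to saying that bias will occur, that it favours either method, or that a form field is missing. The change is a worthwhile low-cost improvement.

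**What to change.** 1. In Section 3.1.1, require the two 30-minute reads of a sample to start as close together as bench capacity allows, or randomise which is read first, inside the existing window. The documents give no basis for a fixed limit in minutes, and scanner capacity is not stated, so the sponsor should set any limit.
2. Record the preparation-end time of each slide and the start of the 30-minute scan of Slide B, or import the scanner timestamp into the eCRF if one exists. If the complete form already holds these fields, say so in the protocol.
3. In Section 4.3.1, report the difference in elapsed time by method. Repeat the hookworm comparison either adjusted for that difference or restricted to closely timed pairs, and extend the existing caution to cover timing.
4. Reconcile the sentence that hookworm eggs disappear within this window with the use of the same window to count them.

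The cost is a few time fields, some bench scheduling and one sensitivity analysis. No additional slides or reads are needed. Reading times that are not captured at the bench may not be recoverable afterwards.
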